# Step Away from Depression—Study protocol for a multicenter randomized clinical trial for a pedometer intervention during and after in‐patient treatment of depression

**DOI:** 10.1002/mpr.1862

**Published:** 2020-11-12

**Keywords:** exercise, mental disorder, MoVo, steps

## Abstract

**Objectives:**

Increasing the number of daily steps by using a pedometer and a diary leads to an activity increase and improved health outcomes in a variety of somatic disorders. Hence, for the inpatient treatment of depression, supervised exercise interventions are more widespread. We aim to examine if a self‐managed pedometer intervention (PI) with the option of being proceeded after discharge leads to reduction of depression and to a physical activity (PA) increase.

**Methods:**

The Step Away from Depression (SAD) study is a multicenter randomized controlled trial targeting 400 patients with major depressive disorder. Treatment as usual (TAU) is compared to TAU plus PI after 4 weeks, at discharge, and 6 months after hospital admission. Primary outcomes are clinically rated depression severity and accelerometer‐measured step counts. Secondary outcomes include self‐reported depression symptoms and PA level, psychiatric symptoms, health‐related quality of life, self‐efficacy, and components of the Motivation Volition Process Model.

**Results:**

We report the design of the SAD study considering several methodological aspects for exercise studies, in general.

**Conclusions:**

Results of our study will provide information about efficacy of PI for inpatient treatment and about interrelating processes of change concerning depression, PA, and aspects of motivation and volition.

## INTRODUCTION

1

### Physical activity and depression

1.1

Depressive disorders are the “largest contributor to nonfatal health loss” (World Health Organization, 2017) worldwide and show a global point prevalence rate of 4.7% (Ferrari et al., 2013). Furthermore, patients with depression are significantly more prone to suffer from somatic disorders, especially chronic diseases (Lotfaliany et al., 2018; Moussavi et al., 2007; Steffen, Nübel, Jacobi, Bätzing, & Holstiege, 2020). Therefore, the effective and long‐lasting treatment of depression remains one of the most challenging issues in mental health care. At present, the German S‐3‐guidelines recommend psychotherapy and/or, according to severity of symptoms, psychopharmacotherapy (DGPPN, 2015). Likewise, from a good clinical practice point, they recommend regular physical activity (PA). Besides therapeutical effects, PA also shows a preventive influence on depression with an adjusted odds ratio of 0.83 (95% CI = 0.79, 0.88; *I*
^2^ = 0.00) for people with higher PA compared to those with lower PA (F. B. Schuch et al., 2018).

PA has been increasingly investigated during the last years with reference to its effectiveness in the treatment of depression. Mutrie, Richards, Lawrie, and Mead (2018) give a detailed overview about current research on this topic. Several meta‐analyses (Cooney et al., 2013; Kvam, Kleppe, Nordhus, & Hovland, 2016; Miller et al., 2020) confirm a small to moderate effect (with effect sizes of *d* = −0,31 up to −0,68) of exercise as a treatment of depression. However, even large effects are demonstrated, showing that underestimation of the exercise‐depression‐effect in the former meta‐analyses may be possible (Ekkekakis, 2015; F. B. Schuch et al., 2016).

### Daily amount of PA in healthy people and in patients with depression

1.2

The World Health Organization (WHO) proposes an amount of 150 min of moderate activity or 75 min of vigorous activity per week or any corresponding combination of these two (World Health Organization, 2010). Moreover, this activity should be executed in time bouts of at least 10 min 63.2% of the overall population of high‐income Western countries comply with these PA sufficiency recommendations (Guthold, Stevens, Riley, & Bull, 2018). Reaching the goal of 10,000 steps per day is still a popular goal in pedometer use (Tudor‐Locke et al., 2011) Healthy people aged 18–65 years usually walk 9797 steps per day (Bohannon, 2007). However, especially concerning low active persons, raising the amount of steps gradually and regularly seems to be more important for health benefit than reaching the goal of 10,000 steps per day (Hallam, Bilsborough, & de Courten, 2018; Lee et al., 2019). Of people with mental disorders, 41.7% fulfill the criteria of the American College of Sports Medicine for PA (30 min of moderate activity on 5 days or 20 min of vigorous activity on three days or 1000 MET minutes in 1 week; Petzold et al., 2017). The percentage of people with depression with insufficient PA seems to be roughly twice as high as that of healthy individuals. Around two thirds (67.8 %) of depressive patients report insufficient PA (F. Schuch et al., 2017). Overall, literature shows that PA self‐report data likely overestimates objective PA (Chaudhury, Stamatakis, Roth, & Mindell, 2010; Garriguet, Tremblay, & Colley, 2015). When only objective measures of PA are taken into account, the percentage of insufficiently active depressive patients even increases up to 85.7. In summary, the figures are alarming and call for interventions to increase daily life PA, even more for people with depressive disorders.

### Walking as a PA intervention

1.3

Pursuing the wider aim of implementing PA interventions in routine care, the following characteristics appear to be reasonable: First, PA interventions have to be easily applicable for patients in an inpatient and outpatient treatment and in a self‐manage setting. Second, taking into account the restriction of financial and human resources in health care as well as the loss of motivation and self‐efficacy that many patients with depression show, exercise interventions for depression should be as simple as possible. Third, the higher prevalence of somatic disorders in patients with depression requires an individual adaptivity concerning the intensity and frequency of PA. In a questionnaire study, depressive patients show a preference for a flexible walking intervention over nine other types of PA like weight lifting, yoga, and dance (Busch et al., 2016). A large and significant effect with a pooled standardized mean difference of −0.86 (with CI of −1.12 to −0.61) compared to control group is shown for walking interventions for depression (Robertson, Robertson, Jepson, & Maxwell, 2012).

One simple and effective tool for increasing walking activity are pedometers. This more objective measure of PA may help to overcome the problem of biased self‐report (Bravata et al., 2007; Tudor‐Locke, Williams, Reis, & Pluto, 2002). The use of pedometers is associated with an increase in PA in healthy subjects, in patients with physical illness or psychiatric diseases (Bravata et al., 2007). Depressive symptoms can be decreased by pedometer use (Abedi, Nikkhah, & Najar, 2015; Piette et al., 2011). Low financial, time, and personnel costs of pedometer interventions (PIs) are important additional reasons to pursue the implementation of this intervention. However, adequately powered randomized controlled clinical trials in patients with major depression are not available in the literature.

### Methodological aspects of PA studies and their consideration in SAD

1.4

#### Collecting data of daily PA

1.4.1

Although studies with PA interventions for depression do report clinical changes, they often fail to do so for a possible change of PA in the patients (Balchin, Linde, Blackhurst, Rauch, & Schonbachler, 2016; Piette et al., 2011). Sometimes, adherence rates to the intervention program are given (Kerling et al., 2015; F. B. Schuch et al., 2015), indicators of body functioning/fitness (e.g., timed walk tests) are presented (Heinzel, Lawrence, Kallies, Rapp, & Heissel, 2015) or weekly feedback is collected (Kerr et al., 2008). It is essential to know whether patients with additional PA interventions move more than patients with treatment as usual (TAU) but with an equal symptom severity of depression after treatment ending.

#### Combination treatment

1.4.2

More research on combination treatments with TAU and TAU + exercise is needed because present findings are not clear concerning the effect size, so far (it has a range of *g* = −0.68 to *g* = −0.08; Kvam et al., 2016). This is mostly due to differences in methodology of the studies and in program variables of the exercise interventions. The effect of exercise decreases with blinded outcome, intent‐to‐treat‐analysis and when compared to guideline TAU.

#### Follow‐up

1.4.3

Many treatments lose their effect after treatment ended and are no longer effective at follow‐up (Cooney et al., 2013; Kvam et al., 2016). For this reason, interventions that are applicable to in‐patient treatment as well as to following self‐management (often in combination with outpatient care) are necessary. Thus, collecting follow‐up data in PA trials is of immense importance.

#### Employing psychological theories

1.4.4

PA interventions which incorporate theories of exercise psychology lead to better results (Thomas, Thirlaway, Bowes, & Meyers, 2020). For this reason, we use the Motivation Volition Process Model (MoVo‐Model; Fuchs, 2007). Whereas many psychological theories of behavior change focus on motivational variables, the MoVo‐Model includes additional postintentional variables. It splits the behavior change process into two phases—the motivational phase (with components like self‐efficacy, outcome expectations, intention strength, and self‐concordance) and the volitional phase (with the components of action planning, barrier management and situational cues). First studies using MoVo‐Model in populations with mental disorders show that the model might be as helpful for the design of interventions in this population as in populations without mental disorders (Petzold et al., 2017). Interventions built on this model lead to promising effects in patients with mental disorders (Gohner, Dietsche, & Fuchs, 2015; Petzold et al., 2019).

#### General methodological aspects

1.4.5

Further methodological aspects such as blindedness of outcome ratings, taking into account anxiety as the most frequent comorbidity of depression and the applicability to real‐life clinical settings were insufficiently put into practice in many former studies (Bond, Stanton, Wintour, Rosenbaum, & Rebar, 2020; Cooney et al., 2013; Kvam et al., 2016). Thus, the need for studies considering these aspects still exists. For the individual patient, even a mildly increased effectiveness of their depression treatment could make a big difference, especially in those with residual symptoms. If successful, our study would give strong empirical support for the use of pedometers to increase PA in patients with major depression during and after inpatient treatment.

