#### Secondary objectives

1.5.2

**Most important secondary objectives** are to compare changes in subjective PA, objective PA, anxiety severity as well as in the duration of in‐patient treatment between PI and TAU.

Further **secondary objectives** are to determine if the PI group differs from TAU group from baseline (first to third day of inpatient treatment) to end of inpatient treatment (three days before end of inpatient treatment) in

psychopathological symptomshealth‐related quality of lifeself‐reported depressive symptomsPA: self‐efficacy, intention, self‐concordance of goal‐striving, outcome expectations, planning, and barrier planninggeneral self‐efficacy

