### Data collection

2.6

Table 1 displays all measurements at different points in time line. All questionnaires are administered in German language.

**TABLE 1 mpr1862-tbl-0001:** Time table of measurements

		T0 (baseline)	T1a (4 weeks)	T1b (discharge)	T2 (follow‐up)
Physical activity					
Objective	Accelerometer measurement for 3 days (primary outcome)	x	x	x	x
Subjective	**Q:** IPAQ short version (7)	x	x	x	x
Adherence	**AD:** Copy of step protocols (IG only)	‐	x	x	x
Depression					
Objective	**I:** Montgomery–Åsberg Depression Rating Scale (primary outcome) (10)	x	x	x	x
Subjective	**Q:** Beck‐Depression‐Inventory II (21)	x	x	x	x
General, physical, and clinical measures					
General measures	**Q:** Sociodemographic data, medication	x	‐	‐	‐
Physiological measures	**HR:** Blood pressure, heart rate, weight, and blood glucose	x	‐	‐	‐
Laboratory values	**HR:** Triglycerides, cholesterol, high density lipoprotein, low density lipoprotein	x	‐	‐	‐
Clinical history	**Q:** Anamnestic questions (6)	x	‐	‐	‐
Psychiatric symptoms	**Q:** Symptom checklist 27 (27)	x	x	x	x
Anxiety	**Q:** Beck anxiety inventory (21)	x	x	x	x
General health quality	**Q:** Short‐Form Health‐Survey 12 (12)	x	x	x	x
Intervention evaluation	**Q:** Questions about the implementation of PI (5)	‐	‐	‐	x
Treatment history	**Q:** Concomitant treatment since discharge (13)	‐	‐	‐	x
Critical life events	**Q:** Social Readjustment Rating Scale (43)	‐	‐	‐	x
Components of the MoVo‐model					
Intention, motivation and volition	**Q:** Intention (2), physical activity specific self‐efficacy (6), outcome expectancies (6), self‐concordance scale (12), action planning (4), coping planning (4)	x	x	x	x

Abbreviations: ( ), number of items; AD, activity diary; HR, information out of hospital record; I, interview; IPAQ, International Physical Activity Questionnaire; MoVo‐Model, Motivation Volition Process Model; PI, pedometer intervention; Q, Online‐Questionnaire or Paper/Pencil.

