#### Anxiety

2.8.3

**Anxiety** symptoms are measured with the Beck Anxiety Inventory (Beck, Epstein, Brown, & Steer, 1988).

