#### Statistical analyses

2.9.2

Accelerometer data are analyzed using Actigraph Software ActiLife 6.13.3. Minimal wearing time is eight hours a day, a PA measure of two complete days serving as minimal criteria to count as valid measurement.

Demographic and clinical characteristics of the study population are reported using descriptive statistics. Differences in baseline values between groups are assessed with chi‐squared tests or Fisher's exact test for nominal data and two‐sample *t*‐tests or Mann–Whitney *U* test for metric/ordinal data scales. Missing data will be imputed by multiple imputation techniques.

For assessing group differences in the primary outcome variables depression and PA, MANOVA is done with IBM SPSS Statistics. If baseline group differences occur (e.g., for age, gender, PA baseline level, comorbidity), we adjust for by analysis of covariance (MANCOVA). Furthermore, we report the percentage of participants in each group meeting criteria of WHO‐recommended PA to provide a benchmark to other PA studies. Likewise, we present remission and response rates for PI and TAU, respectively. Additional subgroup analyses are executed if necessary (e.g., concerning trial site, season of data collection, and medication). If MANOVA shows significant results, single ANOVA and discriminant analysis are executed to investigate the relationship between and the influences on the dependent variables.

Secondary data are analyzed by methods appropriate for the respective scale of the parameter and suitable for specific research questions. Results here are of exploratory nature.

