First, we measure PA objectively (with some constraints: some types of PA cannot be registered correctly or at all like climbing or swimming and wear time cannot be controlled) and subjectively and provide an assessment of depression severity by blinded raters as well as subjectively reported depressive symptomsSecond, the population is generalizable, for being recruited in a naturalistic clinic field in different study centers. Center effects can be analyzedThird, we will provide follow‐up dataFourth, a unique aspect of our PA intervention is that it is personalized and adaptive concerning intensity, length, frequency, and personal circumstances and that is developed based on an empirically supported psychological background. Patients can execute it and continue it afterward in self‐managementFifth, we take into account the effect of comorbid anxiety on our results

Our findings will contribute to the research field of exercise and depression in severely depressed patients and results will give opportunity for refining exercise‐related interventions in inpatient care.

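### The Discussion credits the trial with handling the influence of comorbid anxiety on its findings, but the stated analysis has no anxiety term and admits covariates only after baseline imbalance

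*Protocol article*

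**What the plan says.** All references are to the protocol article.

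- **Section 1.4.5 (General methodological aspects)** names "taking into account anxiety as the most frequent comorbidity of depression" as one of several things that earlier studies did not put into practice well enough. Its parent heading, 1.4, announces how this trial considers such aspects.
- **Section 4 (Discussion)**, fifth strength: "we take into account the effect of comorbid anxiety on our results". No condition and no method are attached.
- **Sections 1.5.2 and 1.5.3** make anxiety an outcome. The leading secondary objectives compare change in "anxiety severity as well as in the duration of" inpatient treatment, and the hypotheses expect less anxiety under the intervention.
- **Section 2.8.3**, under secondary outcome measures: anxiety "symptoms are measured with the Beck Anxiety Inventory". Table 1 schedules the BAI at T0, T1a, T1b and T2.
- **Section 2.9.2 (Statistical analyses)**: "For assessing group differences in the primary outcome variables depression and PA, MANOVA is done with IBM SPSS Statistics". On covariates: "If baseline group differences occur (e.g., for age, gender, PA baseline level, comorbidity), we adjust for by analysis of covariance (MANCOVA"). Subgroup analyses are to be done where needed, with site, season and medication as examples. Secondary data are analysed by suitable methods and are exploratory.
- **Section 2.4.1** stratifies randomisation by center only and discloses allocation after the baseline measurement.

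**The concern.** The fifth strength has a direction: from anxiety to the results. The planned use of anxiety runs the other way, from the intervention to anxiety. An arm comparison of BAI cannot show how anxiety bears on the MADRS or step findings.

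The one stated route by which anxiety might reach the primary model is the imbalance rule, and it is indirect. It names comorbidity rather than anxiety, and it operates only if the arms happen to differ. Imbalance under randomisation is chance. The rule therefore lets the observed data choose the model, and it ignores the better reason for including a covariate, which is that it predicts the outcome.

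At stake is whether a property claimed for the analysis can be found in it. A reader who relies on the fifth strength would expect the primary results to have been examined in relation to anxiety. Under the stated plan, that examination is left to chance imbalance or to a later choice.

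**Working it through.** **1. Claim and method side by side.**

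| Strength in Section 4 | Counterpart in the methods |
|---|---|
| Objective activity measure, blinded depression rating | 2.7.1, 2.7.2 |
| Several centers, center effects | stratification in 2.4.1, site as a subgroup example in 2.9.2 |
| Follow-up data | T2 in Table 1 |
| Personalised, theory-based intervention | 1.4.4, 2.4.3 |
| Influence of comorbid anxiety on the results | BAI measured (2.8.3, Table 1); no unconditional analysis step |

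Only the fifth strength lacks a matching step in the analysis. The wording differs too: center effects are described as something that can be analysed, whereas anxiety is said to be taken into account.

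**2. The plan's own sample size (Section 2.9.1).** Inputs: f² = 0.06, significance level 0.05, power 0.95, stated N = 262, 34% data loss. For two groups and two outcomes the global MANOVA test is an F test with df1 = 2, df2 = N − 3 and noncentrality λ = N·f².

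- At N = 262, λ = 262 × 0.06 = 15.72 and power is 0.951.
- The smallest N with power of at least 0.95 is 261 (stated: 262).
- 262 / (1 − 0.34) = 396.97, so 397 (stated: 396, rounded up to 400).

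The stated figures reproduce to within one patient. The sample size is not at issue and serves only as the reference for the next step.

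**3. Cost of always including T0 BAI.** One covariate takes one degree of freedom, so df2 = N − 4. Let r be the multiple correlation of T0 BAI with the two primary outcomes. The documents do not give it, so 0 to 0.5 is assumed. Adjustment cannot lower the population effect size. It can raise it to at most f²/(1 − r²), reached when the treatment effect lies along the direction in which BAI predicts the outcomes. The table shows that upper limit.

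| assumed r | f²/(1 − r²) | N for power 0.95 | power at N = 262 |
|---|---|---|---|
| 0 | 0.0600 | 261 | 0.951 |
| 0.1 | 0.0606 | 258 | 0.953 |
| 0.2 | 0.0625 | 251 | 0.959 |
| 0.3 | 0.0659 | 238 | 0.967 |
| 0.4 | 0.0714 | 220 | 0.978 |
| 0.5 | 0.0800 | 197 | 0.988 |

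Example at r = 0.5: 0.06 / 0.75 = 0.08 and λ = 262 × 0.08 = 20.96. At r = 0 the lost degree of freedom changes power by less than 0.0001. Actual power at a given r lies between the first row and that row, so unconditional inclusion costs nothing worth counting and may gain some precision.

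**4. What each analysis would answer.** A between-arm comparison of BAI estimates the intervention's effect on anxiety. T0 BAI as a covariate shows how baseline anxiety relates to the outcome and gives an arm effect adjusted for it. Only an arm × T0 BAI term addresses whether the arm effect varies with anxiety. Section 2.9.2 commits to the first only in generic terms, reaches the second only through imbalance, and does not mention the third.

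**The case against.** The strongest reply is that the claim is one line in a list of strengths, not an analysis specification. The lists in Section 2.9.2 are open: comorbidity is an example of a covariate, the subgroups are examples, and secondary data may be analysed in whatever way suits the question. An anxiety analysis fits all of this and may be set out in a full protocol or analysis plan that is not shown. Measuring BAI four times and making it a leading secondary outcome could also count as taking anxiety into account.

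Much of this stands, and it rules out several stronger readings that a reader might infer:

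- *That the trial promised to test whether the intervention works equally well in anxious patients.* It did not. Section 1.4.5 describes earlier studies, and the Discussion sentence does not mention effect modification.
- *That in about 95 of 100 such trials anxiety would never be examined.* This needs a 5% level for the baseline tests, which the article does not give. It also needs comorbidity to mean the BAI score, and all other anxiety analyses to be excluded, which the open wording does not do.
- *That the primary comparison is biased.* Randomisation protects it with or without an anxiety term.
- *That the plan adjusts for anxiety measured after baseline.* Nothing in the article proposes this.

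What does not stand is the reply that measuring and comparing BAI satisfies the sentence, because the sentence concerns the influence of anxiety on the results. Nor is this only silence about detail. Section 2.9.2 states how covariates enter, and that conditional rule does not match an unconditional claim.

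**Conclusion.** The mismatch is real and minor. The Discussion asserts something about the results that the stated analysis does not deliver, except through chance imbalance and a reading of comorbidity that includes anxiety. The consequence is an unsupported strength and a model choice left open, not a wrong primary estimate. An exploratory anxiety analysis remains possible under the current text; it is simply not committed to.

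The correction is nearly free. With 262 analysed, power after adjustment lies between 0.951 and 0.988. The upper figure assumes r = 0.5 and the most favourable alignment of the effect. The mismatch itself rests on the text and does not depend on r.

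**What to change.** In Section 2.9.2, state that T0 BAI is a covariate in the models for MADRS and mean steps whether or not the arms differ at baseline. The T0 value is the right one because it precedes disclosure of allocation. Add an arm × T0 BAI interaction for each of the two outcomes, reported with its confidence interval and labelled exploratory and low-powered, so that it is read by its interval rather than by a significance test.

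If the sponsor does not want this, reword the fifth strength in Section 4 to say only that anxiety is measured and compared between arms as a secondary outcome.

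Cost: BAI is already collected at T0, so no extra data or patients are needed. The first option adds one covariate to each model and one exploratory interaction model per primary outcome. The second changes one sentence. Because recruitment finished in January 2020, the first option should be dated and fixed before the arms are compared, or else reported as post hoc.
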